## Abstract

**Background:**

Myopia has been a rising problem globally. Early-onset myopia significantly increases the risk of high myopia later in life. Despite the proven benefits of increased outdoor time, optimal strategies for preventing early-onset myopia in premyopic children need further investigation.

**Methods:**

This randomized controlled trial aims to evaluate the efficacy of optical (Defocus Incorporated Multiple Segments [DIMS] spectacle lenses) and pharmacological (0.01% atropine eye drops) interventions in preventing myopia among premyopic preschoolers. We will recruit 234 premyopic, asymptomatic 5-to-6-year-old children who will have received cycloplegic autorefraction examination in a countywide kindergarten eye care program in Yilan County, Taiwan. Eligible participants will be randomly assigned to DIMS spectacles (n = 78), 0.01% atropine (n = 78), or usual care (n = 78). In the DIMS group, preschoolers will be instructed to wear spectacles at home before entering elementary school but to wear them all the time after school entry. In the atropine group, subjects will be given 0.01% atropine eyedrops nightly throughout the study period. All participants will be encouraged to spend time outdoors for 2 hours every day. During the 18-month study period, cycloplegic spherical equivalent (SE) refraction, axial length, and subfoveal choroidal thickness will be measured every three months, and parents-administered questionnaires regarding risk factors for myopia will be performed every nine months.

**Primary outcome:**

The change in mean cycloplegic SE.

**Secondary outcomes:**

The cumulative percentage of incident myopia, the cumulative percentage of a fast myopic shift of SE, and the changes in mean axial length.

**Other pre-specified outcomes:**

The time to myopia onset, alteration in subfoveal choroidal thickness, and levels of near work/outdoor activities.

**Trial registration:**

This study is registered at www.clinicaltrials.gov as NCT06200194.

**Conclusion:**

This trial will provide insights into myopia prevention strategies and inform new eye care policies for early identification and intervention in premyopic preschoolers.

## Introduction

Childhood myopia has been a significant public health concern in East Asia for decades. In Taiwan, the prevalence of myopia surged around the school entry age. Myopia has been found in 9.0% - 10.7% of preschoolers aged 5–6 years, and this rate increased to 19.6% - 19.8% among schoolchildren aged seven years [1–3]. It has been reported that juvenile-onset myopia is associated with rapid progression to high myopia in adulthood [4]. High myopia and its complications may pressure the medical care infrastructure and health insurance system significantly. Therefore, it is imperative to adopt strategies to reduce high myopia by delaying the onset of myopia and myopic shift of refractive state among young children at high risk of developing manifest myopia.

The concept of premyopia, defined as a refractive state of an eye of > -0.50 diopters (D) and ≤ 0.75 D in children with other risk factors for myopia, was proposed by the International Myopia Institute in 2019 for myopia prevention [5,6]. It has been reported that mild hyperopia (> +0.5D to ≤ +2.0D), rather than emmetropia, is the typical outcome of refractive development in children [7]. Our previous study revealed that premyopia was the most common refractive status (52%) in Taiwanese preschoolers [8]. Like myopia, premyopia at preschool age was also associated with environmental factors, such as spending more time on screen-based digital devices and less time on outdoor activities [8]. Several longitudinal studies have demonstrated that the single strongest predictor for myopia onset among nonmyopic children is the baseline status of refractive error [9,10]. Young children with premyopia should be the target population for myopia prevention strategies, especially in the post-COVID-19 era. The COVID-19 pandemic has led to changes in children’s learning patterns and lifestyles, causing an increase in myopia prevalence [11–13].

The beneficial effect of increased time outdoors to retard myopia development among schoolchildren has been shown in several clinical trials [14,15]. However, In addition to spending more time outdoors, there are no guidelines or consensus regarding applying other interventions to delay the transition from premyopia to manifest myopia. In the past two decades, various interventions have emerged for controlling childhood myopia, including pharmacological approaches with low-dose atropine and optical approaches like orthokeratology, dual-focus contact lenses, and spectacles with peripheral defocus lenses [16–25]. Only a few studies specifically focused on interventions to delay myopia onset or myopic shift in premyopic children. In Hong Kong, the Low-Concentration Atropine for Myopia Prevention (LAMP2) trial validated the concentration-dependent effectiveness of low-concentration atropine in delaying myopia onset among 4- to 9-year-old children. It was found that the 0.05% atropine group had a significantly lower 2-year incidence of myopia and less myopic shift compared to the 0.01% atropine group and the placebo group [26]. In a small-sample-sized randomized study in India involving 4- to 12-year-old premyopic children, the 0.01% atropine group showed significantly less myopic progression (-0.6 ± 0.3 D vs. -1.75 ± 0.4 D) and axial elongation (0.21 ± 0.2 mm vs. 0.48 ± 0.2 mm) compared to the control group after 2 years [27]. Besides the low-dose atropine, spectacles with peripheral defocus design, such as Defocus Incorporated Multiple Segments (DIMS) lenses, represent another low-side-effect non-invasive treatment of childhood myopia. It may be a promising modality that can be promoted among the high-risk premyopic children. However, a lack of published literature on using DIMS lenses in premyopia warrants further in-depth research.

This clinical trial aims to mainly assess the effectiveness of DIMS spectacle lenses and 0.01% atropine in slowing the progression of myopic spherical equivalent SE among premyopic children before and after elementary school entrance. Because less environmental and academic pressure is presumed at preschool, premyopic children in the DIMS group of this trial will be required to wear DIMS spectacle lenses for near work at home before school entry and full-time after-school entry. This paper aims to describe the rationale, study design, and methods of this clinical trial concerning the optical (DIMS spectacle lenses) and pharmacological (0.01% atropine) approaches for premyopia around the age of elementary school entrance.

## Material and methods

### Study design

To determine the efficacy of different interventions in slowing the SE myopia shift among premyopic children around the school entrance age, we propose to conduct a prospective, randomized, multicenter clinical trial. Two hospitals will participate in this trial: National Yang Ming Chiao Tung University Hospital, and the Yuanshan Branch of Taipei Veterans General Hospital. This trial has been approved by the Institutional Review Board of National Yang Ming Chiao Tung University Hospital (NYCUHIRB No. 2023A018) and registered at www.clinicaltrials.gov as NCT06200194. Informed consent forms will be obtained from the participating children and their parents or guardians. This trial will adhere to the tenets of the Declaration of Helsinki.

### Participants’ recruitment and eligibility

We intend to conduct the recruitment process from September to December 2024, during which the eye care program (the Yilan Myopia Prevention and Vision Improvement Program [YMVIP]) will take place at all kindergartens in Yilan County. The methodology of the YMVIP, involving repeated countywide population-based cross-sectional surveys in Yilan, has been detailed elsewhere [2]. Once premyopic preschoolers are identified through the cycloplegic refraction examination of the YMVIP program, their parents or guardians will be contacted and invited to participate in this trial. The inclusion criteria for this trial are listed as follows:

Age at enrollment: 5–6 years old (the senior grade of kindergarten)Cycloplegic SE of the eye with less SE (less positive or more negative refractive error): < +1.00 D and > -0.50 DAstigmatism: 1.0 D or less in both eyesAnisometropia: 1.50 D or lessMonocular uncorrected visual acuity: 6/7.5 or better in both eyesEither of the parents with moderate myopiaAcceptance of random group allocationSubmission of complete informed consent.

The exclusion criteria are listed as follows:

Strabismus or any ocular motility disorderAny ophthalmic and systemic disorders that might affect visual functions or refractive developmentPrevious treatment of atropine or other myopia control intervention

### Randomization

The eligible participants will be classified into eight strata based on three factors: baseline cycloplegic SE (+0.50 D to < +1.00 D vs >-0.50 D to +0.25 D), gender (male vs female), and parental myopia (one vs two parents). All these factors are associated with myopia development. At the baseline visits, participants in each stratum will be randomly assigned in a 1:1:1 ratio to one of three groups: treatment group 1 (DIMS spectacle lenses), treatment group 2 (0.01% atropine eyedrops), or the control group (usual care). Random allocation will be conducted using a random sequence generated in Excel, with block randomization applied using a block size of 3.

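### A single fixed block size of 3 for three visibly different arms lets anyone who knows the block size and the earlier allocations in a stratum deduce every third allocation

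*Protocol article*

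**What the plan says.** All the allocation rules are in the Randomization section of the protocol article.

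- **Strata:** "The eligible participants will be classified into eight strata based on three factors", namely baseline cycloplegic SE, gender and number of myopic parents. Hospital is not a factor, although under Study design "Two hospitals will participate in this trial".
- **Ratio:** "participants in each stratum will be randomly assigned in a 1:1:1 ratio to one of three groups".
- **Timing:** "At the baseline visits, participants in each stratum will be randomly assigned".
- **Sequence:** "Random allocation will be conducted using a random sequence generated in Excel", "with block randomization applied using a block size of 3". No second or varying block size is mentioned.

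The Intervention section describes spectacles, nightly eyedrops, and usual care with outdoor-time advice. It describes no placebo drops or sham lenses. The article does not use the term open-label, but that the allocation is visible to families and treating staff follows safely from the arms.

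Under Participants' recruitment and eligibility, children are identified at the countywide screening, after which "their parents or guardians will be contacted and invited to participate in this trial". Screening refraction and sex are therefore known before the baseline visit at which the child is randomised.

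**The concern.** Blocking keeps the arms balanced within strata, and the price is predictability. That price is highest when the block is as small as the number of arms and never varies. In a masked trial it matters little, because past allocations are hidden. Here each allocation reveals itself once made, so hiding the list does not stop someone from working out what the list must say next.

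What is at stake is the comparability of the three groups. If staff who invite families or schedule baseline visits can foresee an assignment, they could, knowingly or not, bring a keen family or a child thought to be at high risk forward or hold them back. Differences created this way lie within strata, so stratification does not prevent them.

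**Working it through.** **Inputs from the article:** 3 arms, 1:1:1, block size 3, 8 strata (Randomization); 234 children (Sample size calculation). **Assumptions:** the guesser knows the block size and all earlier allocations in the stratum and names the arm with most places left; the eight strata are equally likely. The article states no figure for predictability, so there is none to reproduce.

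**Within one block.** A block is one of 3! = 6 orderings of the three arms. The chance of a correct guess is 1/3 at position 1, 1/2 at position 2 and 1 at position 3.

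- Certain: 1/3 = 33.3%
- Expected correct: (1/3 + 1/2 + 1)/3 = 61.1%
- By chance: 33.3%

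If every block were complete, this would be 78 of 234 certain and 143 of 234 correct.

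**Allowing for unfinished last blocks.** The mean stratum size is 234/8 = 29.25, and the number left over after whole blocks of 3 averages about 1.

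- Third positions: 8 × (29.25 − 1)/3 ≈ 75.3
- Second positions: 8 × 29.25/3 = 78.0
- First positions: 8 × (29.25 + 1)/3 ≈ 80.7
- Expected correct: (75.3 + 78.0/2 + 80.7/3)/234 ≈ 60.4%

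A simulation of 20,000 trials agrees: mean 75.3 certain, 95% range 74 to 77, and 60.4% correct.

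**If each hospital kept its own list** (16 sequences, an assumption), the mean size is 14.625. Third positions number 16 × (14.625 − 1)/3 ≈ 72.7, and 59.6% are guessed correctly. The result hardly depends on this choice.

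**Alternatives.** The fixed and known sizes are exact over complete blocks. The mixed sizes are simulated with about 29 or 30 children per stratum.

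| Scheme | Certain | Best guess correct |
|---|---|---|
| Fixed 3 | 33.3% | 61.1% |
| Fixed 6 | 20.0% | 56.1% |
| Fixed 9 | 14.3% | 53.2% |
| Random 6/9 | about 5% | about 53% |
| Random 3/6/9 | about 3% | about 54–55% |

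The mixed rows for certainty are cautious: they suppose a guesser who knows which sizes are in use and updates optimally after each child. A larger fixed block lowers certainty but does not come near removing it. Varying the size does, because the guesser seldom knows where a block ends.

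**Balance.** An unfinished block of 3 leaves two arms at most 1 child apart in a stratum; one of 6, at most 2; one of 9, at most 3.

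**The case against.** The strongest reply is that predictability is conditional. Someone must follow allocations in eight strata and, if one list serves both hospitals, at the other site too. The article does not say whether the list is shared or who sees past allocations. This stands, and it is why the condition belongs in the statement of the point. It does not remove the risk: with about 29 children per stratum, a tally is easy to keep.

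Steering by appointment is also less exact than it may seem. Cycloplegic refraction is measured again at the baseline visit, and the article does not say whether the screening or the baseline value sets the stratum. Near the SE cut a scheduler may have only a provisional stratum. Families must also accept random allocation to be eligible. These points weaken the mechanism without closing it.

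The planned GEE adjusts for age, gender, baseline SE, number of myopic parents, near work and outdoor time. Much of any steering by perceived risk would act through these covariates, and the Introduction calls baseline refraction the strongest single predictor of onset. That is a fair limit on the harm. It does not reach unmeasured family motivation, and the ANOVA comparison of 18-month SE change is unadjusted.

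Small blocks have a purpose too: they give the tightest balance within strata.

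A reader might infer three stronger things that the article does not support:

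- **That staff could predict allocations because the size was published.** The article plans recruitment for September to December 2024 and does not show that the size was public then. Trial staff may have known it anyway, but that is not stated.
- **That concealment is absent.** A condensed article may leave who holds and releases the list to the full protocol, so its silence is no finding.
- **That selection bias occurred.** Nothing shows this, and being guessable is not the same as being biased.

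**Conclusion.** The point holds as a weakness in a stated design rule. Under a fixed block of 3, about 75 of 234 allocations can be deduced with certainty and about 60% guessed correctly, given knowledge of the block size and of earlier allocations in the stratum, and assuming equal strata. The rounder figure of 78 would require every block to be complete. List concealment does not change this, because the deduction uses visible past allocations.

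The consequence is an avoidable risk of selection bias. Its effect on the SE difference cannot be sized from the article. The change is worth making because it is cheap, not because the trial is shown to be unsound.

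**What to change.** For allocations still to be made, replace the fixed block of 3 with permuted blocks of randomly varying size, for example 6/9 or 3/6/9, within each stratum, and do not disclose the sizes to recruiting or examining staff. The main gain is in certain allocations, which fall from about a third to about 3–5%. The fall in average guess accuracy, from about 60% to 53–55%, is moderate.

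The cost is a regenerated list and slightly looser balance: up to 3 children's difference between arms in a stratum at the end of recruitment, instead of 1. Sample size, endpoints and treatment are untouched. If all children have already been allocated, the list cannot be changed; the report should then give the block size and acknowledge the limitation.

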### Intervention

Intervention measures include wearing the DIMS spectacle lenses in a stepwise pattern, receiving 0.01% atropine sulfate (0.5-mL unit concentration, preservative-free) once nightly, and maintaining usual care, such as 120 minutes of outdoor activity every day. For all participants, the study staff will emphasize the critical role of increased outdoor time in myopia prevention at each visit. The subjects’ lifestyle and behavior, including outdoor time and time spent on near work, will be recorded in a diary and questionnaire.

#### DIMS spectacle lenses (Treatment group 1)

The DIMS lenses (MiyoSmart, Hoya, Tokyo, Japan) are custom-made plastic spectacle lenses [26]. In this trial, the central optical zone of the DIMS lenses is designed to have no power since the eligible participants have normal uncorrected visual acuity. Unlike the full-time wearing of DIMS spectacle lenses by myopic children, the eligible premyopic participants in this group will be instructed to wear DIMS spectacle lenses part-time until elementary school entrance or until a myopic shift of SE equal to or more than 0.50 D, whichever comes first. In part-time mode, subjects are asked to wear DIMS spectacle lenses after school hours and during weekends and holidays, especially when doing near work. Wearing the spectacles during school hours is not compulsory in the part-time mode. After either entering elementary school or experiencing a myopic SE shift of 0.50 D or more in either eye, the participants will transition to wearing the DIMS spectacles full-time, except during sleep and showers, until the end of the trial. At spectacle dispensing and at each follow-up visit, study staff will provide face-to-face instructions to the subjects and their parents, guardians, or caregivers about the details of spectacle care and the wearing regimen. The use of topical atropine of any concentration will not be permitted for any subject in the DIMS group during the study period.

#### 0.01% Atropine eyedrops (Treatment group 2)

Preservative-free 0.01% atropine eyedrops (AIMedicine, Taipei, Taiwan) will be given to the eligible subjects, with one drop installed in each eye one night before sleeping. If subjects experience significant glare or if their parents are concerned about excessive light exposure during outdoor activities, photochromatic glasses will be offered. Additionally, progressive glasses will be provided if subjects have difficulty with near vision.

#### Usual care (Control group)

In addition to regular eye examinations every three months, study staff will provide face-to-face instructions to the subjects and their parents, guardians, or caregivers at each visit about the importance of adhering to eye care instructions, such as ensuring 120 minutes of outdoor time daily.

### Outcomes and follow-up schedule

In myopia development, cycloplegic SE and axial length are considered the most relevant and reproducible indicators for monitoring refractive changes among young children. Additionally, several factors are associated with myopic shift of SE. Accordingly, we will evaluate primary, secondary, and exploratory outcomes throughout the study period based on the follow-up schedule (Figs 1 and 2).

**Fig 1 pone.0312935.g001:**
[figure not shown]
Schedule of assessment and examination items.

**Fig 2 pone.0312935.g002:**
[figure not shown]
Flow diagram of study design.

Suppose the cycloplegic SE reaches -1.00 D or less in either eye in treatment group 1. In that case, the DIMS spectacle lenses will be replaced with an updated prescription to maintain a corrected visual acuity of 6/7.5 or better. If the same situation happens in treatment group 2 or the control group, single-vision spectacle lenses will be provided with a distance prescription to maintain a corrected visual acuity of 6/7.5 or better.

#### Primary outcome

The primary outcome is the change in mean cycloplegic SE between the baseline visit and subsequent 3-month visits over the study period in each group.

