#### Follow-up schedule

In addition to the baseline visit, all participants will be arranged to have follow-up visits at month 3, month 6, month 9, month 12, month 15, and month 18 after randomization (Fig 1). The subjects in the treatment groups will have additional visits for tolerance assessment in week 2. Most participants will enter elementary school after the first nine months of the follow-up period. The differences in variables of interest between the baseline and each follow-up visit will be analyzed.

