### Statistical analysis

The database of examination parameters and questionnaire items of this study will be constructed with Microsoft Excel software (Redmond, WA, USA). Only the data from the eye with less SE (more myopic or less hyperopic) in each child will be used for identifying refractive status and ocular parameter analysis. Continuous variables will be expressed as mean (SD). Categorical variables will be expressed as frequency and percentage. The independent Student’s t-test, ANOVA, or Pearson’s chi-square test will be adopted to compare the differences between groups in terms of refractive error, demographic characteristics, and questionnaire items. Repeated measures ANOVAs will be used to test the interaction effect of time and treatment for the repeated measures during the follow-up examinations. Statistical analysis will be carried out using IBM SPSS Statistics 26 (IBM Corp., Armonk, N.Y., USA). All p values < 0.05 are considered statistically significant.

For the analysis of the primary outcome, the 1.5-year myopic shift of SE is calculated as the difference in SE between visits at baseline and at Month 18. The changes in SE over the 1.5-year follow-up period will be compared using ANOVA. The post hoc test will be carried out with Bonferroni correction to minimize the potential type I error due to multiple comparisons. The efficacy of myopic shift retardation of the therapeutic intervention is determined by dividing the difference in myopic shift between the treatment group and the control group with the myopic shift in the control group. The intention-to-treat analysis will be adopted to address the issue of loss to follow-up. The missing data in the repeated measures analysis will be dealt with generalized estimating equations (GEE). With one within-subject factor (time), one between-subject factor (treatment assignment) and their interactions, GEE will be employed to determine the treatment effect on the primary outcomes adjusted for some confounding factors, including age, gender, baseline SE, number of myopic parents, time spent on near works and outdoor activities.

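### The primary outcome is given two time frames and two analyses with none named as deciding, and the month-18 ANOVA leaves out the stratification factors

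*Protocol article*

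**What the plan says.** **Time point.** The Abstract names the change in mean cycloplegic SE and gives no time point. The Primary outcome section defines it as "the change in mean cycloplegic SE between the baseline visit and subsequent 3-month visits over the study period", reported for each group. The Follow-up schedule lists those visits: "follow-up visits at month 3, month 6, month 9, month 12, month 15, and month 18 after randomization". It adds that differences from baseline will be analysed at each of them. Statistical analysis is narrower: "the 1.5-year myopic shift of SE is calculated as the difference in SE between visits at baseline and at Month 18". Sample size calculation uses 1-year changes, which is a third time frame.

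**Test.** The primary-outcome paragraph of Statistical analysis says "The changes in SE over the 1.5-year follow-up period will be compared using ANOVA", followed by "The post hoc test will be carried out with Bonferroni correction to minimize the potential type I error due to multiple comparisons". Later in the same paragraph, "GEE will be employed to determine the treatment effect on the primary outcomes", adjusted for age, gender, baseline SE, number of myopic parents, near work and outdoor time. The general paragraph before it says "Repeated measures ANOVAs will be used to test the interaction effect of time and treatment". Every p value below 0.05 counts as significant, and no analysis is ranked above another.

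**Strata.** Under Randomization, "The eligible participants will be classified into eight strata based on three factors": baseline SE, gender and parental myopia. The article says all three are associated with myopia development. The ANOVA includes none of them; the GEE includes all three.

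**The concern.** A confirmatory trial needs one outcome at one time and one test that settles the question. Here the definition and the analysis disagree on the time, and two analyses are each assigned to the primary outcome. They need not agree. The ANOVA is unadjusted and uses the month-18 change, while the GEE is adjusted, uses all visits and is also the stated means of handling missing repeated measures. With 25% dropout expected, the two may rest on different children. If one is significant and the other is not, the article does not say which counts. The Bonferroni correction covers the pairs of arms only, not visits or methods.

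There is also an efficiency loss. Stratifying on prognostic factors balances them across arms. A test that then ignores them leaves their variance in the error term, so its standard errors are too large.

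**Working it through.** **1. The design figures.** The inputs from Sample size calculation are mean changes of -0.17, -0.38 and -0.55 D, SD 0.6, two-sided 5%, 80% power, and 58 evaluable per arm (78 after 25% dropout: 58/0.75 = 77.3, rounded up). The effect size is f = (SD of the three means)/0.6 = 0.259. The noncentral F distribution then gives 49 per arm (147 in total) for 80% power, and 86.8% power at 58 per arm. The stated 174 is therefore not reproduced, but it errs on the large side. That is a separate matter. Below, 58 per arm is used as given.

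**2. Error rate if more than one result may count.** Under independence:
- six visits: 1 - 0.95^6 = 26.5%
- three tests: 1 - 0.95^3 = 14.3%

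The real results are correlated, so null trials were simulated with 58 per arm, six visits, complete data and 4,000 runs per pattern. The three tests were the month-18 ANOVA, the time-by-treatment repeated-measures ANOVA (Greenhouse-Geisser), and a visit-averaged treatment test standing in for the GEE main effect. The correlation patterns are assumptions.

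| Pattern | Month-18 ANOVA alone | Any of 3 tests | Any of 6 visits |
|---|---|---|---|
| Compound symmetry 0.5 | 5.1% | 12.1% | 21.0% |
| Compound symmetry 0.8 | 4.9% | 11.1% | 14.9% |
| Autoregressive 0.8 | 4.2% | 11.9% | 17.5% |
| Autoregressive 0.9 | 5.0% | 12.5% | 13.7% |
| Random slope | 5.2% | 9.0% | 19.2% |

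**3. Leaving out the strata: error rate.** Suppose the strata explain a share R² of the variance and are balanced across arms. Their variance then enters the residual mean square but not the between-arm mean square, so F shrinks by about (1 - R²). The true error rate is about P(F(2,171) > 3.05/(1 - R²)):
- R² = 0.10: 3.6%
- R² = 0.20: 2.4%

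Simulations with and without random dropout from 78 to 58 per arm gave 3.5% to 3.9% and 2.3% to 2.9%. With the strata in the model, the rate was about 5%.

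**4. Leaving out the strata: power.** For DIMS against control the difference is 0.38 D and its standard error is 0.6 × √(2/58) = 0.111, a ratio of 3.41. At alpha 0.05/3 this gives about 84% power when the strata explain nothing. By simulation, with the total SD held at 0.6:

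| R² (assumed) | Unadjusted | Strata in model | Gain |
|---|---|---|---|
| 0.10 | 85% | 88% | about 3 points |
| 0.20 | 86% | 92% | about 6 points |

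**The case against.** The strongest reply is that the article does indicate a lead analysis. Its primary-outcome paragraph fixes month 18 and opens with the ANOVA, and the trial was sized on an ANOVA. Read that way, the error rate is about 5%. This largely stands: it is a fair inference, but no sentence says so, and the GEE sentence claims to determine the treatment effect on the same outcome.

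Three stronger readings are tempting and are not supported.

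- **That the 5% level is already lost.** The 9% to 21% figures need a rule by which any visit or any test may declare success. The text permits that rule but does not state it, and Statistical analysis does not prescribe a separate primary ANOVA at each visit.
- **That three tests are assigned to the primary outcome.** Two are. Repeated-measures ANOVA appears only in the general paragraph, and GEE can be read as the version of that analysis that handles missing data.
- **That omitting the strata invalidates the ANOVA, or costs the full factor 1/(1 - R²) in sample size.** The omission makes the test conservative; it does not inflate error. Stratified allocation already helps the unadjusted test somewhat, so the gain from adjusting is about 3 to 6 points.

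It may also be said that covariate lists and the labelling of supportive analyses belong in an analysis plan. That is reasonable for the detail. It does not excuse two definitions of the primary outcome in one document.

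**Conclusion.** The conflict is in the text. The primary outcome is all six visits in one section and month 18 in another, and both an unadjusted ANOVA and an adjusted GEE are assigned to it without saying which decides. The 5% level is unprotected, though not shown to be lost: about 5% for the month-18 ANOVA alone, 9% to 13% if any of three tests could count, and 14% to 21% if any visit could. These ranges rest on assumed correlations and complete data.

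The omitted strata are the lesser part. If they explain 10% to 20% of the variance, which is assumed because the article gives no figure, the ANOVA runs at roughly 2% to 4% and gives up 3 to 6 points of DIMS-control power. This should be fixed. It is not fatal, because the likely lead test is valid.

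**What to change.** Use the same statement in the Abstract, Primary outcome and Statistical analysis. The primary outcome is the between-group difference in change in cycloplegic SE from baseline to month 18. The deciding test is the month-18 treatment comparison from a model with treatment, baseline SE, gender and number of myopic parents, keeping the Bonferroni correction for the pairs of arms. Label the earlier visits secondary, and the repeated-measures ANOVA and the GEE supportive.

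The GEE should not be made the deciding analysis as it stands. It adjusts for near work and outdoor time, which the Exploratory outcome section lists as outcomes followed over the study and open to influence from the eye care instruction. The GEE sentence does not limit them to baseline values.

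The cost is wording only, since the three covariates are already needed for randomisation. The change should be made and dated before outcome data are examined by arm.
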